### Participant Eligibility and Recruitment

Participants will be recruited using a range of strategies, such as web-based advertising, social media, gambling-related websites, and advertisements in public places such as mental health and addiction services, general practices, and universities. Gambling counseling services and gaming venues across Australia and New Zealand may also assist in participant recruitment. The eligibility criteria are (1) current Australian or New Zealand residence, (2) aged ≥18 years, (3) able to install an app on their own smartphone with internet access, (4) willing to have app notifications activated, (5) English fluency, and (6) seeking assistance for their own gambling. The target population is those with less severe gambling problems who want to adhere to their gambling expenditure limits through the promotion of the app. Consistent with a pragmatic design, there is no requirement to meet any problem gambling diagnostic criteria, and participants are able to engage in other help-seeking activities [56]. However, we will measure the severity of gambling problems using the Gambling Symptom Assessment Scale (G-SAS) [57] to determine the gambling symptom severity of gamblers using the app and explore the degree to which gambling symptom severity influences the efficacy of the intervention.

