In addition to the effect sizes for all primary and secondary outcomes, the metrics of individual-level change will be calculated for all primary and secondary outcomes. Changes beyond that attributable to chance or measurement error will be evaluated using Reliable Change Indices [82], and clinically significant changes [83] will subsequently be calculated at postintervention and 6-month evaluation using functional score ranges where possible (G-SAS score of ≤20 and K6 score of ≤13) or at least a 25% improvement in scores [84]. Participants will be identified as *recovered* (final score falls into the functional range and corresponds to a reliable change), *improved* (final score corresponds to a reliable change but falls into the dysfunctional range), *unchanged* (final score does not correspond to a reliable change), or *deteriorated* (final score corresponds to a relative change in the negative direction).

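### The rule for 'recovered' has no baseline condition, so a participant already in the functional range who reliably improves on the G-SAS or K6 can only be labelled recovered

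*Protocol article*

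**What the plan says.** The last paragraph of Statistical Analyses adds individual-level change metrics to the effect sizes for the primary and secondary outcomes. It uses Reliable Change Indices, then clinically significant change at postintervention and at 6 months. Functional ranges are given for two scales: "G-SAS score of ≤20 and K6 score of ≤13". Where no such range is available, a 25% improvement is used.

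Four classes follow, introduced by "Participants will be identified as" and with no restriction on who is classified:
- *Recovered*: "final score falls into the functional range and corresponds to a reliable change".
- *Improved*: the change is reliable, yet the participant still ends on the dysfunctional side of the cut-off.
- *Unchanged*: no reliable change was made.
- *Deteriorated*: a change in the negative direction.

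Participant Eligibility and Recruitment says "The target population is those with less severe gambling problems" and that "there is no requirement to meet any problem gambling diagnostic criteria". None of the six eligibility criteria refers to a G-SAS or K6 score. The G-SAS is measured to describe severity and to explore its influence on efficacy.

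**The concern.** Recovery ordinarily means moving from the dysfunctional to the functional range. The written rule checks only where the participant ends and whether the change is reliable; it does not check where the participant began. In a trial that screened for severity above the cut-off this would do no harm, because everyone would start dysfunctional. This trial has no such screen, says it is aimed at milder gambling problems, and has no entry condition on distress.

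The class *recovered* would then mix two groups: those who crossed the cut-off, and those who were never above it and improved further. A recovery figure for the G-SAS or K6 would depend partly on how mild the enrolled sample happened to be.

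**Working it through.** **Step 1: the rule by cases.** The protocol states no recovery figure to reproduce, so the check is logical first. Take reliable change to mean improvement, since worsening has its own class.

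| Baseline | Final | Reliable improvement | Class under the written rule |
|---|---|---|---|
| Dysfunctional | Functional | Yes | Recovered |
| Dysfunctional | Dysfunctional | Yes | Improved |
| Functional | Functional | Yes | Recovered |
| Either | Either | No (and no worsening) | Unchanged |

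The third row is the problem. *Improved* is barred because the final score is not dysfunctional, *unchanged* because the change is reliable, and *deteriorated* by direction. This needs no assumed number.

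**Step 2: one participant.** Reliable-change threshold = 1.96 × SD × √(2 × (1 − reliability)). SD and reliability are not in the document. With an assumed G-SAS SD of 9:
- reliability 0.90: 1.96 × 9 × √0.20 = 7.9 points;
- reliability 0.80: 1.96 × 9 × √0.40 = 11.2 points.

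A participant going from 19 to 7 falls 12 points, which is reliable at either value. That participant was never above 20 and is labelled recovered.

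**Step 3: how often.** The document gives no baseline mean, SD, reliability, pre-post correlation or scale range, so all inputs here are assumptions. Scores are simulated as correlated normal pairs, rounded and clipped to the scale, with reliability 0.87 and correlation 0.5.
- G-SAS: range 0–48, SD 9, mean fall 6, threshold 1.96 × 9 × √0.26 = 9.0.
- K6: range 0–24, SD 5, mean fall 2, threshold 1.96 × 5 × √0.26 = 5.0.

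| Scale, baseline mean | Functional at baseline | Recovered as written | Recovered, dysfunctional baseline required | Share of the recovered who were never dysfunctional |
|---|---|---|---|---|
| G-SAS 18 | 61% | 35% | 21% | 41% |
| G-SAS 22 | 43% | 33% | 24% | 26% |
| G-SAS 26 | 27% | 28% | 24% | 15% |
| G-SAS 30 | 15% | 21% | 19% | 8% |
| G-SAS 34 | 7% | 14% | 13% | 4% |
| K6 9 | 82% | 29% | 10% | 64% |
| K6 13 | 54% | 27% | 18% | 34% |
| K6 16 | 31% | 22% | 18% | about one in six (16–17%) |

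The middle three percentages are of all participants.

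**Step 4: a different change model.** Here change is independent of baseline.
- G-SAS (SD 9, baseline means 18–26, reliability 0.8–0.9, mean fall 4–8, SD of change 8): the share is about 26% to 59%.
- K6 (SD 5, baseline means 8–13, reliability 0.8–0.9, mean fall 2, SD of change 4.5): about 51% to 83%.

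The size is sensitive to the model as well as to the baseline mean.

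**Step 5: direction.** At G-SAS mean 22, 24.4% of all participants recover from a dysfunctional start, and 1 − 0.435 = 56.5% start dysfunctional. Recovery among those who could recover is 0.244 / 0.565 = 43%, against 33% of everyone under the written rule. The rule counts too many people as recovered, yet a percentage over all participants can be lower than the rate among those able to recover.

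**The case against.** The strongest reply is about rank. These classes supplement the effect sizes. The primary proximal outcome is adherence to expenditure limits, the primary outcome of the within-group evaluation is expenditure, and G-SAS and K6 are secondary in an uncontrolled follow-up. No stated hypothesis uses recovery status. All of this stands: a reader might take the recovery percentages for headline results, and the document does not present them so.

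A reader might also infer that the denominator is wrong. The protocol states no recovery percentage and no denominator. It says only that participants are classified, and the reporting base may be set in an analysis plan that is not shown. Nor does the document support saying that the figures could not be compared with other trials, since how those trials classify participants is not at hand.

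The article is condensed and cites a method for clinically significant change, so the four definitions may be shorthand for a rule that includes a baseline condition. That is possible, but the classes are written out in full and as written they force the label. An unseen source cannot be used to add a condition.

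Finally, the size is assumed. Milder gambling problems are tied to no G-SAS score, participants must be seeking help for their gambling, and baseline distress is not described. It may be tempting to say that many participants will start within the G-SAS range and most within the K6 range; the document does not establish either.

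**Conclusion.** The point holds as a defect in a stated rule. Any participant functional at baseline who reliably improves on the G-SAS or K6 is classed as recovered, and the eligibility criteria do not exclude such participants. This follows from the text alone.

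Its reach is limited to the supplementary individual-level metrics on the two scales with stated functional ranges, at postintervention and 6 months. The microrandomized comparison and the GEE analyses are untouched.

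Its size is open. With reliability 0.87 and correlation 0.5, it is small if the sample is severe (about 4–8% of the recovered at G-SAS means 30–34) and substantial if it is mild (41% at mean 18; 64% on the K6 at mean 9). A reader might conclude that the trial's recovery results will simply be inflated. Step 5 shows that this does not follow for the percentage; what follows is that the class contains people who had no dysfunctional range to leave.

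**What to change.** In the last paragraph of Statistical Analyses:
- define *recovered* as a baseline score in the dysfunctional range (G-SAS above 20; K6 above 13), a reliable improvement, and a final score in the functional range;
- say where reliable improvers who were functional at baseline go, either in a class of their own or under *improved* (both work; the choice should be fixed before the data are seen);
- report the recovery percentage among participants dysfunctional at baseline, with that number shown for each scale.

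The cost is about one sentence. No new data are needed, because a reliable change cannot be calculated without the baseline score. The downside is that fewer participants carry the label and the percentage rests on a smaller denominator, which could be quite small for the K6 if baseline distress is low.

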### Ethics Approval

This trial has been approved by the Deakin University Human Research Ethics Committee (2020-304) and prospectively registered with the Australian New Zealand Clinical Trials Registry (ACTRN12622000497707).

## Results

The development and evaluation of *Gambling Habit Hacker* was a collaboration between Deakin University, University of Auckland, Turning Point, and 2and2 (app developers) and funded in June 2019 by the New South Wales Government’s Responsible Gambling Fund. In line with JITAI development recommendations [43], a multidisciplinary team was created to draw on behavior change expertise from clinical and social psychology, implementation science, biostatistics, and research design, in conjunction with smartphone app developers. The development of the treatment content was led by the first author ([name]) and is part of a broader program investigating implementation planning for addictive behaviors. The app is hosted on the Cogniss behavior change platform created by 2and2, a custom technology solution developer. Illustrative screenshots of this JITAI are displayed in Figure 2.

**Figure 2 figure2:**
[figure not shown]
Illustrative screenshots of the *Gambling Habit Hacker* app.

Following an extensive development period, *Gambling Habit Hacker* was subjected to user testing of app functionality between June 2021 and July 2021 with 14 gambling experts. The testers included gambling counselors (n=5), gambling researchers (n=5), and people with lived experience (n=4). Consumers were 3 men and 1 woman, with an average score on the Problem Gambling Severity Index in the problem range (mean 13.0, SD 9.1). Testers used the app on Android and IOS devices for a 3-day period and provided quantitative and qualitative feedback on acceptability, usability, and quality. Quantitative evaluation was performed using the Mobile App Rating Scale [80], which comprises 23 items across 4 subscales measuring perceived engagement, look and feel, functionality, and quality. Experts were reimbursed with an Aus $50 (US $34) e-gift voucher for their time.

Quantitative evaluation indicated that all scores were higher than the minimum acceptability score of 3, which suggests that the app may be helpful [85] (Multimedia Appendix 3). Intervention content was rated highly in terms of strategy relevance to plan creation (>7 out of 10), helpfulness of strategy description (almost 8 out of 10), and quotes on lived experience were perceived as helpful (>7 out of 10). Experts rated planning functionality highly (>7 out of 10) and indicated slightly lower scores for helpfulness of information in coping planning (>6 out of 10). The lowest rated items were TimeLine Follow-Back (calendar to assess past-month gambling behavior) and TimeLine Follow-Forward (calendar to assess planned gambling behavior over the next month), where ease of completion was rated as just over 3 out of 10. Qualitative data were generally positive in terms of comprehensiveness and quality of information, credibility, graphics, and interactivity. The main issues raised were related to functionality in terms of loading times, errors in the notification schedule, and difficulty in entering and saving data in the timeline calendars. The evaluation also indicated that the participant burden needed to be reduced in terms of the length of pretrial measures and the time required to complete the EMA items. Technical issues, including user acceptability concerns, were addressed through extensive redevelopment of the calendars, reducing the number of items in the baseline and EMAs, and correcting the schedule of notifications. A total of 3 testers subsequently used the app again and confirmed that the issues had been satisfactorily resolved.

The user testing phase of the app-administered action planning and coping planning as separate interventions, where coping planning was delivered 30 minutes after action planning and only where participants indicated that they had not implemented their action plan. User testing revealed that this was confusing and was an added burden, which meant most participants did not complete coping plans even if they were assessed as eligible (ie, they had not implemented the action plan). In response to this finding, we merged action- and coping planning as a single intervention delivered concurrently (without a time delay).

The empirical data gathered as part of this trial will be used to optimize the JITAI and to make it more efficient, effective, and scalable. The app is available for download in Australia and New Zealand for Apple (App Store) and Android (Google Play Store) devices. Following its release on the app stores, a total of 7 pilot participants were recruited to check all protocols, and the functionality was operated as intended. Advertising commenced on April 11, 2022, and as of May 26, 2022, a total of 36 participants were recruited for the trial. The trial is expected to conclude in early 2023 with results published mid-2024.

## Discussion

### Overview

Preliminary findings suggest that *Gambling Habit Hacker* is acceptable and feasible for adhering to gambling expenditure limits. To the best of our knowledge, this study is the first to examine the effectiveness of real-time support for implementation planning activities to adhere to gambling expenditure limits. Using an MRT design, this trial will determine if real-time action- and coping planning are more effective than no intervention in adhering to gambling expenditure limits (primary proximal outcome), and using a within-group evaluation, it will determine whether there are reductions in gambling expenditure (distal primary outcome). Consistent with the HAPA model and implementation planning literature, participants are encouraged to specify their gambling intentions (using the TimeLine Follow-Foward) and then use tailored planning to identify opportunities to act. This information will be used to optimize the content of the next version of *Gambling Habit Hacker* in line with recommendations for digital behavior change methods and JITAI development [43,86,87].

Consistent with recommendations [43,87], *Gambling Habit Hacker* is based on well-established behavior change frameworks that delineate intentional and volitional phases, targeting the volitional phase. It is also based on the BCT of goal setting (TimeLine Follow-Forward) with BCTs for specific steps of planning and self-regulation incorporated within the intervention. EMA items are drawn from areas consistently associated with gambling lapses, such as urges and high-risk situations. The EMI content of the active components is designed from the planning literature, specifically examining action- and coping planning. The MRT design allows the evaluation of the intervention components within each subject, providing enhanced statistical power to explore the efficacy of the intervention on real-time variations in behavioral outcomes. All communications within the app are aligned with the self-determination theory, whereby the app offers real-world stories by way of developing relatedness, offers personalized goal setting and planning (autonomy), and provides repeated attempts to practice planning, as well as the identification of barriers that can improve the individual’s chances of adhering to their limits (competence).

Similar to previous studies [36,40], it is proposed that the structure of this intervention could be relevant to any behavior change. We selected adhering to gambling expenditure limits as the proximal goal to be attained, and the strategies presented have come from gamblers’ reports on how to adhere to gambling limits and the associated challenges. EMAs assess the presence of internal and situational cues for unplanned gambling; however, the app design could be adapted to other behaviors where threats to adhering to limits have been identified. The planning framework would remain the same across any health behavior.

Little is known about hourly, daily, or weekly fluctuations in the strength of individuals’ gambling goals or the experience of internal or situational cues associated with unplanned gambling. Although this work will provide such knowledge, there is a risk that the timing and frequency of the EMAs (3 times per day) may be too few on some days and too many on others or that the timing is not aligned with high-risk situations. For example, evening EMAs conclude at 8 PM even though the risk of being in a gambling venue may be outside these hours. Following this, there is a chance that a limited number of EMI-eligible moments will be identified. Although designed for low burden, the repetitive nature of EMA items may lead to low engagement and automatic responses to questions or dropouts. While planning activities are undertaken within the app, implementing the plan is done *in the real world*. A subsequent limitation is that the completion of activity after planning cannot be monitored.

### Dissemination of Findings

The results of this trial will be disseminated to peer-reviewed journals, conference presentations, and stakeholder forums. Plain language findings will be disseminated to participants who indicate an interest in the study findings. Participants can access the findings on project websites [88,89].

### Conclusions

The aim of *Gambling Habit Hacker* is to provide evidence-based, real-time support for individuals wishing to adhere to their gambling expenditure limits. Through the use of the app, individuals’ cognitive burden in identifying, evaluating, selecting, and operationalizing an appropriate option is reduced. The app and associated algorithms present appropriate strategies in line with personalized real-time EMA outcomes.

## Appendix

Multimedia Appendix 1 Tailoring variables collected in the time-based ecological momentary assessment.

Multimedia Appendix 2 Summary of Gambling Habit Hacker time points for components and measures.

Multimedia Appendix 3 User testing: Gambling Habit Hacker expert evaluation scores (n=14).

## Abbreviations

BCT: behavior change technique
EMA: ecological momentary assessment
G-SAS: Gambling Symptom Assessment Scale
HAPA: Health Action Process Approach
JITAI: Just-In-Time Adaptive Intervention
MRT: microrandomized trial
